| 
 
To evaluate ventilator-free days and incidence and duration of any form of new ventilation use.
 
                                                                                                                                                                                                                     | 
 
Duration (days) of ventilation and ventilation-free days.
 
Incidence of any form of new ventilation use and duration (days) of new ventilation use.
 
                                                                                                                                                                                                                                                                                                                                                                                                                                                                                                                                                                                                                                                                                                                                                                                                                                                                                                                                                     |

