| 
 
To evaluate intensive care unit (ICU) and hospitalisation length.
 
                                                                                                        | 
 
Duration (days) of ICU and hospitalisation.
 
                                                                                                                                                                              |
| 
 
To evaluate National Early Warning Score 2 (NEWS2).
 
                                                                                                                      | 
 
NEWS2 assessed daily while hospitalised and on Days 15 and 29.
 
Time to a NEWS2 of <math>\leq 2</math>, maintained for at least 24 hours.
 
                                                                        |
| Exploratory                                                                                                                                                                                                                |                                                                                                                                                                                                                                                                            |
| 
 
To evaluate SARS-CoV-2 viral load.
 
                                                                                                                                       | 
 
Qualitative and quantitative PCR determination of SARS-CoV-2 in blood and saliva (while hospitalised) on Days 1, 3, 5, 8, 11, 15, and (optional) Day 29 (may become a secondary endpoint once the assays are available).
 
 |
| 
 
To collect samples for translational research on host and viral genomics, serum antibody production, COVID-19 diagnostics, and validation of laboratory testing methods.
 
 | 
 
Analysis of samples collected at baseline prior to treatment and at specific time points.
 
                                                                                                                                |

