## 8.1 Efficacy Assessments

### 8.1.1 Improvement on the 9-Point Scale

For the purposes of this study, the condition of each potential participant in the study will be assessed using a 9-point category ordinal scale:

0. Uninfected, no clinical or virological evidence of infection
1. Ambulatory, no limitation of activities
2. Ambulatory, limitation of activities
3. Hospitalised – mild disease, no oxygen therapy
4. Hospitalised – mild disease, oxygen by mask or nasal prongs
5. Hospitalised – severe disease, noninvasive ventilation or high-flow oxygen
6. Hospitalised – severe disease, intubation and mechanical ventilation
7. Hospitalised – severe disease, ventilation and additional organ support – vasopressors, renal replacement therapy (RRT), extracorporeal membrane oxygenation (ECMO)
8. Death

For Grade 5, ‘high-flow oxygen’ consists of a heated, humidified high-flow nasal cannula delivering up to 100% heated and humidified oxygen at a maximum flow of 60 L/minute via nasal prongs or cannula to a patient at rates of flow higher than traditional low-flow therapy. In high-flow oxygen, the fraction of inspired oxygen (FiO2) can be titrated from 21% to 100% independent of the flow rate.

Note: If initial data suggest that there are too few patients in certain categories, the decision may be made to combine parts of the ordinal scale, leading to a smaller number of categories.

To be considered for inclusion in the study, patients must be Grade 3 to 5 on this scale.

To be considered a “responder” to treatment with a target candidate, a patient needs to show an improvement of at least 2 points (from randomisation) on this scale. For example, a patient who is Grade 5 (hospitalised - severe disease, noninvasive ventilation or high-flow oxygen) at randomisation but improves to Grade 3 (hospitalised - mild disease, no oxygen therapy) would be considered to be a responder. A patient with a live discharge from hospital or who is considered fit for discharge (a score of 0, 1, or 2 on the ordinal scale) will also be considered to be a responder.

The primary endpoint will be time to clinical improvement of 2 points (from randomisation). The response rate (number and percentage of patients) will be determined for each treatment arm (target candidate) on Days 2, 8, 15, 22, and 29 as a secondary endpoint.

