### **8.1.2 Other Efficacy Assessments**

Overall mortality will be assessed on Days 15, 29, and 60, and, where applicable, time from treatment (candidate agent) start date to death will be calculated.

The duration (days) of oxygen use and oxygen-free days (to Day 29) will be a secondary endpoint.

The duration of mechanical ventilator-free days (to Day 29) will be a secondary endpoint, as will be the incidence and duration (days) of new mechanical ventilation use.

The duration (days) of intensive care unit (ICU) and hospitalisation will also be a secondary endpoint.

The National Early Warning Score 2 (NEWS2) has demonstrated an ability to discriminate patients at risk of poor outcomes. This score is based on 6 physiological measurements (respiration rate, oxygen saturation [SpO2], systolic blood pressure, pulse rate, level of consciousness or new confusion, and temperature), and the overall score is uplifted by 2 points for patients requiring supplemental oxygen to maintain their recommended SpO2. For patients confirmed to have hypercapnic respiratory failure on blood gas analysis, on either a prior or their current hospital admission, and requiring supplemental oxygen, the following are recommended: (i) a prescribed SpO2 target range of 88% to 92%, and (ii) that the dedicated SpO2 scoring scale (Scale 2) on the NEWS2 chart should be used to record and score the SpO2 for the NEWS2. NEWS2 will be assessed daily while hospitalised and on Days 15 and 29. This should be evaluated at the first assessment of a given study day.

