| Secondary   | 
Stage 1:
 
2-point improvement on a 9-point ordinal scale will be analysed using CMH test, with stratification factors as covariates.
 
Time to live discharge.
 
Stage 2:
 
Binary endpoints, including response rates at Days 2, 8, 15, 22, and 29, and mortality rates at Days 15, 29, and 60, will be analysed using the same CMH test and logistic regression model as in the primary endpoint.
 
Time-to-event endpoints, including time to clinical improvement, time to death, and time to live discharge, from treatment start date will be plotted with Kaplan-Meier curves and will be tested with the log-rank test.
 
Other continuous endpoints will be summarised with descriptive statistics such as mean, standard deviation, median, minimum, and maximum.
                                                                                                                                                                                                                                                                                                                                                                                                                                                                                                                                                                                                                                                                         |

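### Ventilation is defined two ways across the secondary endpoints, and ICU and hospital stay are listed only as raw durations that early death can shorten

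*Protocol*

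**What the plan says.** **Ventilation.** The secondary endpoints in the Protocol synopsis and in Table 1 (Section 3.0) include duration of ventilation and ventilation-free days, with no qualifier, and "Incidence of any form of new ventilation use and duration (days) of new ventilation use". Section 8.1.2 describes the same endpoints differently: "The duration of mechanical ventilator-free days (to Day 29) will be a secondary endpoint", together with "the incidence and duration (days) of new mechanical ventilation use". The ordinal scale in Section 8.1.1 keeps the two kinds of support apart. Grade 5 reads "Hospitalised – severe disease, noninvasive ventilation or high-flow oxygen", and intubation with mechanical ventilation begins at Grade 6. Grade 5 is an eligible baseline grade (Section 5.1).

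**Durations.** Table 1 lists "Duration (days) of ICU and hospitalisation". Section 8.1.2 repeats this: "The duration (days) of intensive care unit (ICU) and hospitalisation will also be a secondary endpoint". Neither gives a window or a free-days measure. Oxygen has both: "The duration (days) of oxygen use and oxygen-free days (to Day 29) will be a secondary endpoint". Ventilation also has a free-days measure to Day 29. For Stage 2, Table 4 analyses the remaining continuous endpoints by description: "Other continuous endpoints will be summarised with descriptive statistics such as mean, standard deviation, median, minimum, and maximum".

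**Death.** The protocol does not say how a patient who dies counts in any duration or free-days measure. Its only non-completer rule, in Section 9.5.4, concerns response rates, and that section leaves further missing-data detail to the SAP.

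**The concern.** The two parts are separate faults.

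On ventilation, an SAP cannot follow both texts. New ventilation use, its duration and ventilation-free days all change with the definition. The affected patients are common by design, since noninvasive ventilation lies within an eligible baseline grade and one step above Grade 4.

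On ICU and hospital stay, a raw duration treats leaving by death and leaving by recovery alike. If an agent caused early deaths and did nothing else, its duration summary could come out shorter than that of standard of care. The summaries are descriptive, but they are not without influence. Section 9.5 has efficacy results summarised by stage. Section 9.6 bases progression to Stage 2 on the totality of data and allows the Stage 2 primary endpoint to be reconsidered from Stage 1 results.

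**Working it through.** **1. Ventilation: the texts side by side.** The last column reads mechanical ventilation as the scale does, that is, Grade 6 and above.

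| Patient | Synopsis and Table 1 (any form) | Section 8.1.2 (mechanical) |
|---|---|---|
| Grade 4 at baseline, starts noninvasive ventilation | New-use event; the days count as ventilated | No event; the days count as ventilator-free |
| Grade 5 at baseline on noninvasive ventilation, never intubated | Ventilated from baseline | Never ventilated; every day counts as free |
| Grade 3 or 4 at baseline, intubated directly | New-use event | New-use event |

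The texts agree only in the last row. Incidence, duration and free days can therefore all differ with the section followed.

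**2. ICU and hospital stay: what death does to a raw duration.** The protocol gives no mean, SD or mortality for these endpoints, so there is no figure to reproduce and every input below is an assumption. Let survivors stay L days in both arms, deaths occur on Day t, and mortality be m.

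Mean stay = (1 − m) × L + m × t

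With L = 14 and t = 7:
- m = 10%: 0.9 × 14 + 0.1 × 7 = 13.3 days
- m = 20%: 0.8 × 14 + 0.2 × 7 = 12.6 days

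The arm with more deaths appears 0.7 day shorter although survivors are identical. In this two-value example the median stays at 14 days in both arms, because more than half the patients survive.

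In general, the shift is (extra mortality) × (t − L). For L from 10 to 20 days, t from Day 3 to Day 7 and 5 to 15 percentage points more deaths:
- smallest: 0.05 × (7 − 10) = −0.15 day
- largest: 0.15 × (3 − 20) = −2.55 days

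**3. The same example as days alive and out of hospital.** Over the 28 days from Day 1 to Day 29, with death scored 0, a survivor has 28 − 14 = 14 days.
- m = 10%: 0.9 × 14 = 12.6 days
- m = 20%: 0.8 × 14 = 11.2 days

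The arm with more deaths is now 1.4 days worse.

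**4. The existing free-days measures.** Take ventilator-free days over 28 days, survivors ventilated V = 4 or 8 days, a ventilated patient dying on Day t = 3 to 7, and 5 to 10 points more deaths.
- Scored as 28 minus ventilated days, the shift is (extra mortality) × (V − t). It runs from 0.10 × (4 − 7) = −0.3 to 0.10 × (8 − 3) = +0.5 day.
- With death scored 0, the shift is −(extra mortality) × (28 − V). It runs from −0.05 × (28 − 8) = −1.0 to −0.10 × (28 − 4) = −2.4 days.

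Without a scoring rule, even the direction is open. With death scored 0, it is harm throughout.

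**The case against.** The strongest reply is that silence is not a rule. The protocol nowhere says that a death contributes a short, favourable value. Scoring of deaths is commonly settled in the SAP, which is not at hand. This stands for oxygen-free and ventilator-free days. It does not fully answer the point on ICU and hospital stay, where choosing a raw duration as the only measure is a decision the protocol itself makes. Death is also an observed outcome rather than missing data.

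The second reply is that safeguards exist, and this stands. Time to live discharge is a secondary endpoint tested by log-rank, and a death in hospital cannot count as a live discharge. Mortality at Days 15, 29 and 60 and time to death are analysed in their own right. ICU stay has no counterpart to live discharge, so it is the more exposed of the two.

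Third, mechanical ventilation might be read loosely to include noninvasive support, which would remove the conflict. The scale's own wording goes against this, and nothing in Section 8.1.2 says so.

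A reader might infer more than the documents support:
- That the durations are judged on means alone. Table 4 also lists the median, standard deviation and range, and attaches no test.
- That the plan makes early death count as benefit. It leaves this possible but does not fix it.
- That the ventilation conflict produces the death problem. The two are unrelated.
- That Grade 5 prevents noninvasive ventilation from being separated from high-flow oxygen. The scale cannot separate them, but footnote d of the schedule of activities (Section 1.3) records ventilator requirement and start and stop of each form of support.

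**Conclusion.** The ventilation inconsistency is a plain contradiction between the synopsis and Table 1 on one side and Section 8.1.2 on the other. It does not depend on the SAP, and the passages must be reconciled. Its numerical effect cannot be given, because the protocol does not say how many patients are expected to receive noninvasive ventilation without intubation.

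The point on ICU and hospital stay holds as a weakness in the choice of measure, not as an error in a test. Early deaths can shorten the descriptive summary, by 0.7 day in the single illustration and by 0.15 to 2.55 days over the range tried. This assumes that survivors are identical in both arms and that deaths come earlier than the typical survivor's departure. If deaths came as late as survivors' departures, the shift would vanish. The conclusion that a harmful agent would pass as beneficial is not supported, because mortality and time to live discharge are tested alongside.

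**What to change.** 1. In the synopsis, Table 1 and Section 8.1.2, use one definition of ventilation for duration, free days and new use. If the other is wanted, report it as a separately named item. Both can be derived from the start and stop data under footnote d, so the cost is wording only.
2. For ICU and hospital stay, report days alive and out of ICU, and days alive and out of hospital, to Day 29, with patients dead by Day 29 scored 0. State the same scoring for the existing oxygen-free and ventilator-free days.
3. Keep the raw durations as description only, shown by survival status.

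The derivations use ICU, hospital and survival dates that the listed endpoints already require. The price is a composite that is slightly harder to interpret than a length of stay, since a low value can mean a long stay or a death. Showing it beside mortality and the raw durations deals with most of that. No added hypothesis test is needed.

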### 9.5.2 Safety Analyses

#### Analysis of adverse events

All AEs reported in this study will be coded using the currently available version of the Medical Dictionary for Regulatory Activities (MedDRA). Coding will be to lowest level terms. The preferred term (PT), and the primary system organ class will be listed.

Summaries of all treatment-emergent adverse events (TEAEs) by treatment group will include:

- The number (n) and percentage (%) of patients with at least 1 TEAE by system organ class and PT
- TEAEs by severity, presented by system organ class and PT
- TEAEs by relationship to treatment (related, not related), presented by system organ class and PT
- Treatment-emergent AESIs (defined with a PT or a prespecified grouping)

Deaths and other SAEs will be listed and summarised by treatment group.

TEAEs leading to permanent treatment discontinuation will be listed and summarised by treatment group.

### **Analysis of clinical laboratory evaluations**

The number and proportion of patients with normal/abnormal laboratory tests or different grades on Days 3, 5, 8, and 11 (or day of discharge) will be presented as shift tables by the baseline status (Day 1).

### **Analysis of vital signs**

Potentially clinically significant abnormality (PCSA) values are defined as abnormal values considered medically important by the Sponsor according to predefined criteria/thresholds based on literature review. The incidence of PCSA vital signs on Days 8, 15, and 29 (or day of discharge) will be summarised overall and by their baseline normality status (normal/abnormal).

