| Targeted physical examination (focused on lung auscultation)                                       |                    |                        | X                                 |                                  |                                  |                                                 |                                                    |
| Vital signs, including temperature, pulse rate, blood pressure, respiratory rate, SpO 2 |                    | X c         | X                                 | X                                | X                                |                                                 |                                                    |

|                                                                                                                               | Screening       | Baseline         |                                                  |                               |                               |                                           |                                              |
|-------------------------------------------------------------------------------------------------------------------------------|-----------------|------------------|--------------------------------------------------|-------------------------------|-------------------------------|-------------------------------------------|----------------------------------------------|
| Day (± Window)                                                                                                                | Day -1 or Day 1 | Day 1            | Daily Until Hospital Discharge                   | Day 15 a (±2 days) | Day 29 a (±3 days) | Day 60 a (±4 days) (Follow-up) | Day 90 a (±6 days) (End of Study) |
| Clinical assessments d                                                                                             |                 | X c   | X                                                | X                             | X                             |                                           |                                              |

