| Haematology, chemistry, liver function tests, coagulation f                                                        | X g  | X c,h | Days 3, 5, 8, 11 (all ±1 day) while hospitalised |                               |                               |                                           |                                              |
| Pregnancy test for females of childbearing potential                                                                          | X g  |                  |                                                  |                               |                               |                                           |                                              |
| RESEARCH LABORATORY                                                                                                           |                 |                  |                                                  |                               |                               |                                           |                                              |
| Blood (SST) for exploratory inflammatory cytokine analysis (others to be defined in sub-protocols)                            |                 | X                | Day 8                                            | X                             | X                             |                                           |                                              |
| Blood (sodium heparin tube) for PBMC phenotyping i                                                                 |                 | X                | Day 8                                            | X                             | X                             |                                           |                                              |
| Blood (EDTA) for SARS-CoV-2 PCR (qualitative and quantitative)                                                                |                 | X                | Days 3, 5, 8, 11 (all ±1 day) while hospitalised | X                             | X                             |                                           |                                              |

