| Blood (EDTA) host genome (host DNA) j                           |                 | X        |                                                  |                               |                               |                                           |                                              |
| Mid-turbinate nasal swab viral genome j                         |                 | X        |                                                  |                               |                               |                                           |                                              |

EDTA=ethylenediaminetetraacetic acid; FiO2=fraction of inspired oxygen; PBMC=peripheral blood mononuclear cell; PCR=polymerase chain reaction;

PO2=partial pressure of oxygen; RT PCR=reverse transcription polymerase chain reaction; SARS-CoV-2= severe acute respiratory syndrome coronavirus 2;

SoC=standard of care; SpO2=oxygen saturation; SST=serum separator tube.

Note: Additional assessments, if required, will be defined in the sub-protocol.

a These visits will be performed even if a patient has already been discharged. If discharged prior to scheduled visit, in-person visits are preferred, but recognising that quarantine and other factors may limit the patient's ability to return to the clinic, these visits may be conducted by telephone or with a home visit by study staff. For visits conducted by telephone, it will not be possible to perform some scheduled assessments (eg, vital signs). The Day 29 assessments will also be performed, where possible, for patients who discontinue the study prematurely.

b Medical history includes estimated date and time of first symptoms and number of co-morbidities (eg, respiratory, cardiovascular, metabolic, malignancy, endocrine, gastrointestinal, immunologic, renal).

c Baseline assessments should be performed prior to study drug administration.

d Includes ordinal score, National Early Warning Score 2 (NEWS2), oxygen requirement, noninvasive or invasive ventilator requirement, including start and stop of low- or high-flow oxygen supply or of any form of ventilation etc.

e If done as part of SoC, blood gases results to be fully recorded with date and time.

f For parameters, see [Table 5](#).

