| 
 
To evaluate response rate (see primary endpoint for definition of responder).
 
                                                                                            | 
 
Response rate (number and %) by treatment arm at Days 2, 8, 15, and 29.
 
                                                                                                                                                  |
| 
 
To evaluate time to discharge.
 
                                                                                                                                           | 
 
Time to live discharge from the hospital.
 
                                                                                                                                                                                |
| 
 
To evaluate overall mortality.
 
                                                                                                                                           | 
 
Mortality at Days 15, 29, and 60.
 
Time from treatment start date to death.
 
                                                                                                                                      |
| 
 
Change in the ratio of the oxygen saturation to fraction of inspired oxygen concentration (<math>\text{SpO}_2/\text{FiO}_2</math>),
 
                                      | 
 
<math>\text{SpO}_2/\text{FiO}_2</math>, measured daily from randomisation to Day 15, hospital discharge, or death
 
                                                                                                        |
| 
 
To evaluate the safety of candidate agents as add-on therapy to SoC in patients with COVID-19.
 
                                                                           | 
 
Physical examination.
 
Clinical laboratory examinations.
 
Vital signs (blood pressure/heart rate/temperature/respiratory rate).
 
Adverse events.
 
                                                 |

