- **Stage 2** of the study (confirmation) is intended to provide confirmatory data of the identified candidate agents from Stage 1, to fully evaluate disease outcomes, including severe AEs, overall AEs, disease-related co-infection complications (eg, pneumonia, septic shock), and overall mortality in an expansion stage. Patients and outcomes from Stage 1 will not form part of Stage 2.

Some candidate agents will still be in Stage 1 of the study at the point where other candidate agents have progressed to Stage 2.

Patients will be randomised to receive one of the candidate agents that is being evaluated at the time of randomisation and whose inclusion/exclusion criteria they meet (as an add-on to SoC) or to a control arm where only SoC is administered.

In each stage of the study, patients will be screened on Day -1 or Day 1, and will remain in the clinic from Day 1 until fit for discharge. Dosing with the candidate agent (as an add-on to SoC) will commence on Day 1. The last day of assessments while hospitalised will be on Day 29. An outpatient visit will be conducted on Day 60 ( $\pm 4$  days), with an end-of-study visit conducted on Day 90 ( $\pm 6$  days).

Enrolment of patients will be continuous throughout the study for each candidate agent until the total randomisation number of planned patients for Stage 1 and Stage 2 is achieved. Enrolment under a sub-protocol for a specific candidate agent may also be stopped in the event of success or failure of the candidate agent. The Master Protocol will continue enrolling patients as long as there are candidate agents that are enrolling. It is estimated that up to 1800 patients will participate in the overall study.

Study centres will be located in the United Kingdom. Overall, it is estimated that approximately 18 centres and investigators will initially take part in the study.

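### Vital signs are recorded daily in hospital from Day 1, but the abnormal-value table in Section 9.5.2 leaves out Days 2–7 for every patient still in hospital on Day 8

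*Protocol*

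**What the plan says.** **Collection.** The vital-signs row of the example Schedule of Activities (Protocol Section 1.3; "Vital signs, including temperature, pulse rate, blood pressure, respiratory rate" and SpO2) is marked at the Day 1 baseline, in the column headed "Daily Until Hospital Discharge", and at Days 15 and 29. Vital signs are listed among the secondary safety endpoints in Table 1.

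**Exposure.** Section 4.1: "Dosing with the candidate agent (as an add-on to SoC) will commence on Day 1".

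**Analysis.** Section 9.5.2, Analysis of vital signs: "The incidence of PCSA vital signs on Days 8, 15, and 29 (or day of discharge) will be summarised", overall and by whether the baseline value was normal. The section names no any-time or worst-value summary.

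**Visits after discharge.** Footnote a of the schedule keeps the Day 15 and Day 29 visits for discharged patients, prefers them in person and allows a home visit or a telephone call. It adds: "For visits conducted by telephone, it will not be possible to perform some scheduled assessments (eg, vital signs".

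**Laboratory rule, for comparison.** Section 9.5.2 says laboratory results "on Days 3, 5, 8, and 11 (or day of discharge) will be presented as shift tables". The schedule takes the post-baseline safety bloods on "Days 3, 5, 8, 11 (all ±1 day) while hospitalised".

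**The concern.** A candidate agent given from Day 1 may disturb blood pressure, pulse, temperature or respiration in the first days of dosing. The protocol collects the daily readings that would show this, but the one vital-signs table it specifies begins at Day 8. The laboratory rule in the same section does use Days 3 and 5. Vital signs are thus measured more often than bloods in the first week, yet summarised later.

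Two of the three named days are also the ones most exposed to loss, since a patient seen by telephone on Day 15 or 29 has no vital signs.

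Stage 1 is meant to give a preliminary view of safety in about 60 patients per arm. An excess of abnormal readings confined to Days 2–7, among patients still in hospital on Day 8, would not appear in the PCSA table.

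**Working it through.** The protocol gives no figure for this point, so there is none to reproduce. The check sets the schedule against the summary rule and counts days.

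**Inputs**
- Days collected: Day 1, daily to discharge, and Days 15 and 29 (Section 1.3).
- Days summarised: 8, 15 and 29, or day of discharge (Section 9.5.2).
- Dosing from Day 1 (Section 4.1).

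**Step 1: first week.** Days 2–7 are 7 − 2 + 1 = 6 post-baseline days. A patient in hospital on Day 8 has a Day 8 reading, and any discharge day is Day 8 or later. So 0 of 6 enter the table, however the discharge-day clause is read.

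**Step 2: in-hospital days that enter, by length of stay.** Post-baseline in-hospital days = last hospital day − 1. The text does not say whether the discharge day replaces a missed day or is added, so a range is shown where this matters.
- Discharge Day 5: 1 of 4.
- Discharge Day 7: 1 of 6.
- Discharge Day 10: 1 or 2 of 9. Day 8 always enters. Day 10 enters if the clause adds a day, or if it stands in for a missing Day 15 or 29 value.
- Discharge Day 15: 2 of 14.
- Stay to Day 29: 3 of 28 = 10.7%.

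Patients who have left may also contribute Day 15 and Day 29 values if seen in person or at home. Those values do not restore any of Days 2–7.

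**Step 3: what six unsummarised days could hold.** The documents give no daily PCSA probability. Assume a constant probability q per day, independent between days. The chance of at least one PCSA value on Days 2–7 is 1 − (1 − q)^6:
- q = 2%: 1 − 0.98^6 = 11.4%
- q = 5%: 1 − 0.95^6 = 26.5%
- q = 10%: 1 − 0.90^6 = 46.9%

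For patients still in hospital on Day 8, none of these readings enters the table. Independence is a simplification. An abnormality that lasts to Day 8 would still be seen there, so the loss is greatest for short-lived ones.

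**Step 4: why a crude any-time count is not enough.** Take q = 5% in both arms, so there is no treatment effect. With discharge on Day 5 (4 days observed), any-time incidence is 1 − 0.95^4 = 18.5%. With discharge on Day 10 (9 days) it is 1 − 0.95^9 = 37.0%. The rate per observed day is 5% in both. An any-time summary therefore needs its observation time beside it.

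**The case against.** The strongest reply is that this is one table and that first-week signals have other routes.
- Section 9.5 provides for safety results to be listed and summarised by scheduled time where appropriate, and daily vital signs are scheduled.
- Adverse events are evaluated daily. Under Appendix 4 an abnormal vital sign that the investigator judges clinically significant is an adverse event.
- NEWS2, built largely from vital signs, is scored daily in hospital. SpO2/FiO2 is measured daily to Day 15, discharge or death.
- Progression to Stage 2 rests on the totality of data (Section 9.6), and the IDMC reviews safety throughout (Section 9.7.2). Nothing makes the PCSA table a gate.
- A SAP, not shown here, could add an any-time display.

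Much of this stands. A reader might infer that first-week vital signs are lost to the trial altogether; the documents do not support that.

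The other routes are still not equivalent. The adverse-event route depends on investigator judgement in an unblinded study, and Appendix 4 leaves out disease-associated findings unless more severe than expected. NEWS2 is a composite efficacy score, and SpO2/FiO2 covers oxygenation only. The wording in Section 9.5 is conditional and does not promise a PCSA comparison. Nor is this a detail left open for the SAP: the protocol names the days.

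A reader might also infer that patients who leave early are judged only on their discharge day. Footnote a rules that out as a general statement, because the Day 15 and Day 29 visits still take place and in-person attendance is preferred.

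**Conclusion.** The point holds for the PCSA table. For every patient still in hospital on Day 8, 0 of 6 first-week post-baseline days enter it, and a stay to Day 29 contributes 3 of 28 days (11%). These counts follow from the schedule and Section 9.5.2 alone. The percentages in Step 3 are illustrations that rest on an assumed, constant and independent daily probability.

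It is tempting to go further and say that the discharge-day clause tilts the comparison towards an agent that shortens stay, since patients tend to be well on the day they leave. That direction is an inference. The documents give no vital-sign values by day and do not say how the clause operates. What they support is narrower: the clause is undefined, and the rule leaves collected first-week safety data out of the only vital-signs analysis that Section 9.5.2 specifies. This should be changed, but it does not by itself undermine the Stage 1 decision.

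**What to change.** In Section 9.5.2, Analysis of vital signs:
1. Add the incidence of at least one PCSA value at any post-baseline assessment to Day 29, using the daily values already collected in both arms.
2. Show it by fixed window (Days 1–7 after the baseline reading, 8–14, 15–29), with patients and days observed per arm and a rate per observed patient-day. The first window is the least affected by differences in length of stay. In later windows those still in hospital are a selected group, and a rate does not remove that selection.
3. Keep the Day 8/15/29 table as supplementary, with the number of patients who have a value on each day, so that telephone visits are visible.
4. State whether the discharge day replaces a missed day or is added.

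For the laboratory shift tables, only reconcile the discharge-day clause with the schedule, which has no discharge-day sample. A worst-value rule drawing on all routine-care results is not recommended. Footnote h is attached to the Day 1 laboratory cell and covers only tests within the visit window.

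Cost: protocol wording and more table programming, with no new assessments. Reported incidence will be higher than under the present rule, and the report should say why.
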